### Inclusion criteria

The patients met the diagnostic criteria of DPD in “Guidelines for the Diagnosis and Treatment of Depression, Anxiety and Psychotic Disorders in Parkinson’s Disease” (31).Age range of 50 to 75 years old.According to the evaluation by the PD-specific outpatient department of the project cooperation unit, the patient has received standardized medication for at least 3 months, has a fixed anti-PD drug treatment plan, and has no drug adjustment plan for the next 3 months.H–Y staging ≤2.5 levels (the guidelines for the diagnosis of PD in China define patients with H–Y stage ≤2.5 as early PD patients) (32).Hamilton Depression Rating Scale (HAMD-17) >7 points, and ≤24 points.The patients have not received acupuncture treatment for DPD or PD in the past 3 months.No language and intellectual disabilities Mini-Mental State Examination (MMSE), able to complete DPD-related scales assessments.Participating voluntarily in the study and have signed informed consent to treatment.

### Exclusion criteria

Patients with secondary Parkinson’s syndrome or Parkinson’s superposition syndrome.Patients who are currently taking or have taken traditional antidepressants in the past 2 weeks, such as selective serotonin and norepinephrine reuptake inhibitors (venlafaxine, etc.), selective serotonin reuptake inhibitors (sertraline, paroxetine, fluoxetine, citalopram, etc.), tricyclic antidepressants (amitriptyline, etc.).Patients undergoing neurosurgical surgery (deep brain stimulation), psychological therapy, or repeated transcranial magnetic stimulation therapy.Patients with serious internal medical conditions such as heart, liver, kidney, hematopoietic system disorders malignant tumors, as well as mental disorders.Patients are unable to undergo an fMRI scan for other reasons.

### Randomization and blinding

All DPD participants will be randomly assigned in a 1:1 ratio to one of two groups: the control group and the acupuncture group. Random numbers will be generated by an independent researcher using PROC PLAN in SAS 9.2 (SAS Institute, Cary, NC, United States). The random numbers will be sealed in opaque envelopes by an independent research assistant. Once the random allocation principle is accepted, participants will randomly select an opaque envelope to receive an allocation serial number. The number will then be documented on a case report form (CRF) by a research assistant specifically assigned to this task. To preserve blinding, the acupuncturist, researchers, assessors, and statistical analysts will be kept separate throughout the study. Because of the specific nature of acupuncture treatment, it is not possible to blind the acupuncturists during the treatment. Before the study begins, acupuncturists will be trained uniformly. They will be asked not to disclose the grouping to their patients.

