### Sample size calculation

In this study, the sample size was calculated using G*Power 3.1 software, and the HAMD-17 response rate was selected as the primary outcome. We also designed a pre-trial. The results of our pre-trial study showed that the response rate of DPD in the acupuncture group was 92%. When conducting a one-sided significance test, the ratio of the two groups is 1:1, and the setting of *α* = 0.05, *β* = 0.80. The calculated preliminary sample size is 78 patients. Considering a dropout rate of 10%, and a corrected sample size of 87 cases. Ultimately, 88 patients will be included, with 44 patients in each group.

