### Data management and quality control

At baseline, information on the patient’s age, gender, occupation, education level, dominant hand, medical history, etc. We will arrange for patients who meet the inclusion criteria to undergo questionnaire evaluation in a quiet room with no unrelated personnel, followed by an fMRI examination. All fMRI will be conducted using the same 3.0 T MRI machine.

The case report form (CRF) that has been approved on ethical grounds will be used to collect clinical data on each enrolled patient. The data from the paper CRF forms will be entered into a Microsoft Excel spreadsheet independently by two researcher assistants. A comparison of the data entry results between the two research assistants will be conducted to identify any inconsistencies. Any discrepancies in the electronic data will be validated by a third independent research assistant who will review the paper data. The electronic data will be analyzed using SPSS 20.0 software (IBM Corporation, Armonk, NY, United States).

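### Free choice of envelope leaves the order of assignment unfixed, so a returned or exchanged envelope would not show when drawn numbers are checked against the generated list

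*Protocol article*

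**What the plan says.** All of the procedure is in the protocol article under Randomization and blinding.

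- Ratio: "All DPD participants will be randomly assigned in a 1:1 ratio to one of two groups: the control group and the acupuncture group".
- Generation: "Random numbers will be generated by an independent researcher using PROC PLAN in SAS 9.2".
- Concealment: "The random numbers will be sealed in opaque envelopes by an independent research assistant".
- Assignment, once the patient has agreed to be randomized: "participants will randomly select an opaque envelope to receive an allocation serial number".
- Recording: "The number will then be documented on a case report form (CRF) by a research assistant specifically assigned to this task".
- Separation of roles: "To preserve blinding, the acupuncturist, researchers, assessors, and statistical analysts will be kept separate throughout the study".

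The same section states that acupuncturists cannot be blinded. The primary outcome (Primary indicator) is the proportion of patients whose HAMD-17 total falls by at least 50% by week 12. The target is 88 patients, 44 per group (Sample size calculation). Recruitment is already under way (Progress of research). No block size, and no blocking of any kind, is mentioned.

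**The concern.** Concealment by envelope works best when the next assignment is fixed before the next patient is known. Numbered envelopes opened in list order do this: the patient at a given place in the enrolment order must receive the assignment at that place in the list, and any departure is visible. The article describes a different rule, in which the participant picks any envelope from those available. No particular envelope is then the correct one, so no departure from the correct one can be seen.

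The stake is protection against selection bias. If a draw were returned or exchanged because someone preferred another arm for that patient, the arms could differ in prognosis, and the analysis could not identify or undo it. The safeguard matters more here than in a double-blind trial, because the acupuncturists know the arm and the primary outcome is a rating scale.

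This is a rule that the article states, not a detail that a condensed article has left out.

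**Working it through.** The plan gives no figure on this point to reproduce. Two questions decide it: is the free draw still random, and what can a later check detect?

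**Inputs.** Two arms at 1:1 (Randomization and blinding); 88 patients, 44 per arm (Sample size calculation). Assumption: the envelope pool is exactly 44 + 44, drawn without replacement.

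**Step 1: is the draw random?** Suppose k envelopes are gone, a of them acupuncture.

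- Free draw: the chance that the next is acupuncture is (44 − a)/(88 − k).
- List order, when the list is a random permutation of 44 + 44 without blocks: the chance is also (44 − a)/(88 − k).

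The two schemes therefore have the same distribution. After 44 enrolments the acupuncture count has, under either scheme,

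SD = √[44 × 0.5 × 0.5 × (88 − 44)/(88 − 1)] = √(11 × 0.506) = √5.56 = 2.36.

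A simulation of 20,000 runs agrees:

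| Scheme (unblocked list) | Final split | Mean absolute between-arm difference after 44 | 95th percentile |
|---|---|---|---|
| Free draw | 44/44 in every run | 3.7 | 10 |
| List order | 44/44 by construction | 3.7 | 10 |

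Leaving the list order does not in itself bias allocation.

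**Step 2: what can be reconciled?** The generated numbers are what the envelopes contain, and the drawn number is written down for each patient. Afterwards one can check that each patient has a number, that each number is used at most once, and that each number corresponds to the arm on the list.

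**Step 3: what would that reconciliation miss?** Take envelope i (acupuncture) and envelope j (sham). A patient draws i, it goes back into the pool, and the patient is given j. A later patient draws i.

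| Check | Free draw | Numbered envelopes opened in list order |
|---|---|---|
| Each patient has a number | passes | passes |
| Each number used once | passes | passes |
| Number matches its arm on the list | passes | passes |
| Number matches place in enrolment order | cannot be applied, because no order was fixed | fails, and so reveals the exchange |

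Only the fourth check detects the exchange, and free selection removes it.

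**Step 4: blocking.** If the generated list is blocked, balance within blocks holds only when the list is followed in order. Free selection would lose it. The article states no blocking, so this is conditional. The final split of a fully used 44 + 44 pool would be unaffected in any case.

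**The case against.** The strongest reply is that the main elements of concealment are stated: independent generation, independent sealing, opaque envelopes, a dedicated recorder and separated roles. A blind draw from a fixed pool is unpredictable and ends 44/44. The article describes no re-drawing, and an envelope log, custody and signatures are operational details that it may leave to a fuller protocol. All of this stands, and it limits the point to a weak safeguard. It does not remove the point, because free selection is the stated rule, and under that rule even a complete record of the final numbers lacks the one check that would reveal an exchange.

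A reader might infer more than the documents support:

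- **That the computer list is abandoned, or that allocation cannot be audited.** The generated numbers are what is sealed, and each drawn number is recorded. Patient, number and arm can be reconciled; only the order of assignment cannot.
- **That writing the number on the CRF unblinds the assessors.** The CRF "will be used to collect clinical data on each enrolled patient", but nothing says that the serial number discloses the arm. A dedicated assistant records it, and roles are kept separate. Any coded identifier could be decoded by someone holding the key.
- **That free selection costs a measurable amount of balance compared with, say, blocks of 4.** No blocking is stated, so that comparator would be invented. Setting the SD of 2.36, which is for an arm count, beside a limit of 2 on the between-arm difference would also mix two scales. On the count scale, blocks of 4 would give exactly 22 of 44. Imbalance partway through recruitment does not measure selection bias either.

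**Conclusion.** The point holds as a weakness of safeguard. Under the stated rule the order of assignment is not fixed in advance, a returned or exchanged envelope would pass reconciliation against the list, and any blocking would be lost.

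The documents do not show that any exchange has occurred or that the allocation is biased. They give no rate of re-draws from which to estimate an effect, so no size can be put on it. There is no consequence for the sample size, alpha or the planned analysis. The equivalence in Step 1 assumes an unblocked 44 + 44 pool and a truly random pick.

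The change is worth making promptly, because recruitment is running and the safeguard cannot be added afterwards for patients already allocated. It is not a defect that by itself puts the trial's validity in doubt.

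**What to change.** 1. Have the independent holder of the list number the remaining sealed envelopes in the order of the PROC PLAN list.
2. Open strictly the next number, and only after eligibility and baseline assessments are complete.
3. Write the participant ID and the date on the envelope before it is opened.
4. Keep the allocation log apart from the CRF.
5. For patients already enrolled, report that participants selected their own envelopes and state from which patient the new procedure applied.

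The cost is relabelling the unused envelopes and a short amendment. The number of patients, the significance level and the analysis stay as they are. Sequential opening does not make an exchange impossible, but it leaves a visible mismatch between number, date and enrolment order.

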### Interventions

The treatment will receive 36 acupuncture treatments (three times a week) within 12 weeks. Hwato brand disposable acupuncture needles (0.30 × 25 mm or 0.30 × 40 mm in size) will be used.

For the acupuncture group, acupuncture needles will be inserted into acupoints Baihui (GV20), Naohu (GV17), Fengfu (GV16), bilateral Fengchi (GB20), Dazhui (GV14), Shendao (GV11), Zhiyang (GV9), Mingmen (GV4), and Yaoyangguan (GV3) (Figure 2; Table 2). The acupuncture procedure is as follows: the patient is placed in a prone position and undergoes routine skin disinfection, needles (size 0.30 × 25 mm) will be inserted obliquely into Baihui (GV20), Naohu (GV17), and vertically into Fengfu (GV16), bilateral Fengchi (GB20) with a depth of 8–10 mm. After eliciting deqi, the needles will be used for twirling-rotating manipulation. The needles (size 0.30 × 40 mm) will be inserted vertically into Dazhui (GV14), Shendao (GV11), Zhiyang (GV9), Mingmen (GV4), and Yaoyangguan (GV3) with a depth of 10–15 mm. After eliciting deqi, the needles will also be used for twirling-rotating manipulation. Every acupoint requires a 30 s needle manipulation and a 30 min needle retention.

**Figure 2 fig2:**
[figure not shown]
Location of acupoints or sham acupoints in the trial. GV20, Baihui; GV17, Naohu; GV16, Fengfu; GB20, Fengchi; GV14, Dazhui; GV11, Shendao; GV9, Zhiyang; GV4, Mingmen; GV3, Yaoyangguan; SA, sham acupoint.

For the control group, we chose the sham acupoint method. The reason why we choose sham acupoint therapy instead of non-invasive therapy is that Chinese patients generally have acupuncture and moxibustion treatment experience, and DPD patients often have strong anxiety and distrust of people and things around them.

It is recommended that sham acupoints be located in areas that are not in proximity to effective acupoints for the treatment of PD and depression. The head acupoints are associated with the central nervous system and are located where meridians are densely distributed to minimize the physiological effects. The sham acupoints were selected as 1 cm on each side of the midpoint of the line connecting Xiaoluo (SJ12) and Naohui (SJ13), 1 cm lateral to the midpoint of the line connecting Naohui (SJ13) and Jianliao (SJ14), and 1 cm on each side of the midpoint of the line connecting Yinmen (BL37) and Fuxi (BL38) (Table 3). After routine disinfection of the skin, needles that are 25 mm long and 0.18 mm in diameter will be oblique needling into sham acupoints at a depth of 2–4 mm. Do not have deqi and lifting, inserting, twisting, and turning. The needles will be kept in place for 30 min.

**Table 2 tab2:** Location of acupoints used in the acupuncture group.

	Acupoints	Location	Angle	Depth
1	Baihui (GV20)	5 cun directly above the midpoint of the anterior hairline, or at the midpoint of the line connecting the apexes of the two auricles	45°	8–10 mm
2	Naohu (GV17)	At the top of the head, there is a depression located at the upper edge of the external occipital protuberance	45°	8–10 mm
3	Fengfu (GV16)	On the nape, directly below the external occipital protuberance, lies a depression between the trapezius muscles on both sides	90°	10–15 mm
4	Fengchi (GB20)	On the nape, below the occiput, at the depression between the upper portions of the sternocleidomastoid and trapezius muscles	90°	10–15 mm
5	Dazhui (GV14)	On the midline of the back of the neck, at the depression below the spinous process of the 7th cervical vertebra	90°	10–15 mm
6	Shendao (GV11)	On the midline of the back, at the depression below the spinous process of the 5th lumbar vertebra	90°	10–15 mm
7	Zhiyang (GV9)	On the midline of the back, at the depression below the spinous process of the 7th thoracic vertebra	90°	10–15 mm
8	Mingmen (GV4)	On the midline of the waist, at the depression below the spinous process of the 2nd lumbar vertebra	90°	10–15 mm
9	Yaoyangguan (GV3)	On the midline of the back, at the depression below the spinous process of the 4th lumbar vertebra.	90°	10–15 mm

**Table 3 tab3:** Location of sham acupoints used in the control group.

	Sham acupoints	Location
1	Sham acupoints 1	1 cm to the right of the midpoint of the line connecting Xiaoluo (SJ12) and Naohui (SJ13) points
2	Sham acupoints 2	1 cm to the left of the midpoint of the line connecting Xiaoluo (SJ12) and Naohui (SJ13) points
3	Sham acupoints 3	1 cm to the lateral to the midpoint of the line connecting Naohui (SJ13) and Jianliao (SJ14)
4	Sham acupoints 4	1 cm to the right of the midpoint of the line connecting Yinmen (BL37) and Fuxi (BL38)
5	Sham acupoints 5	1 cm to the left of the midpoint of the line connecting Yinmen (BL37) and Fuxi (BL38)

### Sample size calculation

In this study, the sample size was calculated using G*Power 3.1 software, and the HAMD-17 response rate was selected as the primary outcome. We also designed a pre-trial. The results of our pre-trial study showed that the response rate of DPD in the acupuncture group was 92%. When conducting a one-sided significance test, the ratio of the two groups is 1:1, and the setting of *α* = 0.05, *β* = 0.80. The calculated preliminary sample size is 78 patients. Considering a dropout rate of 10%, and a corrected sample size of 87 cases. Ultimately, 88 patients will be included, with 44 patients in each group.

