##### Primary indicator

The response rate (The response rate, defined as the proportion of total scores that decreased by at least 50% compared with baseline statistics) of HAMD-17 (at week 12).

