### Statistical analysis

#### Clinical data analysis

Statistical analysis will be conducted utilizing SPSS 20.0 (IBM Corporation, Armonk, NY, United States), a software package to analyze statistical data. Statistical significance was determined at the 0.05 level (two-tailed). The intention-to-treat (ITT) analysis will be employed as the primary analysis for all patients, and missing data were filled in using the last observation carried forward (LOCF). A supplementary analysis will be conducted using the adherence protocol analysis (PP).

The categorical data will be described using frequencies and percentages. The proportion of patients with progression ≥0.5 grades compared to the baseline of H–Y staging, and adverse events were analyzed using the chi-squared test. The initial step in the analysis of continuous data is to assess their normality. The data are described using mean ± standard deviation or median (interquartile range). Within-group comparisons are conducted using either paired *t*-tests or Wilcoxon signed-rank tests, while between-group comparisons are carried out using independent samples *t*-tests or Mann–Whitney *U* tests. HAMD-17, QIDS-SR, UPDRS-III, and PDQ-39 were analyzed using either repeated-measures ANOVA or a generalized linear mixed model based on repeated measurements.

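### The 78 patients are computed for a one-sided 0.05 test but significance is judged two-tailed at 0.05; if 78 was derived as stated, the intended 80% power is about 70%, and the primary ITT/LOCF analysis may move it further

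*Protocol article*

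**What the plan says.** **Sample size calculation.** The primary outcome is the HAMD-17 response rate, and G*Power 3.1 was used. The only response rate given comes from a pre-trial study: "the response rate of DPD in the acupuncture group was 92" per cent. No control rate appears. The test is described thus: "When conducting a one-sided significance test, the ratio of the two groups is 1:1", "and the setting of *α* = 0.05, *β* = 0.80". Then: "The calculated preliminary sample size is 78 patients". The dropout step follows: "Considering a dropout rate of 10%, and a corrected sample size of 87 cases". The total is: "Ultimately, 88 patients will be included, with 44 patients in each group".

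**Clinical data analysis.** "Statistical significance was determined at the 0.05 level (two-tailed"). No separate rule is given for the primary outcome. The same section makes ITT the primary analysis, with missing values filled by LOCF and a per-protocol analysis as a supplement.

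**Primary indicator.** Response at week 12 is "defined as the proportion of total scores that decreased by at least 50% compared with baseline statistics".

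**Table 1 and the Abstract.** HAMD-17 is taken at baseline and at weeks 12, 24 and 48. No HAMD-17 visit is listed between baseline and week 12.

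**The concern.** The sample size belongs to one test and the trial will be judged by another. A two-sided 0.05 test needs a larger observed difference than a one-sided 0.05 test, so a size that gives 80% power for the second gives less for the first. A null result on the primary outcome would then be read as coming from a trial with 80% power when it had clearly less. Leaving both statements in place also leaves room to choose the sidedness after the data are seen.

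A second mismatch lies in the dropout allowance. Dividing 78 by 0.9 assumes that dropouts leave the analysis and the rest show the full effect. Under ITT with LOCF they stay in. With no score after baseline before week 12, the value carried forward is the baseline itself, a 0% fall, which is a non-response by the plan's own definition. That lowers both response rates and narrows the difference between them.

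**Working it through.** **Inputs from the protocol.** Acupuncture rate 0.92; one-sided α = 0.05; intended power 0.80; 78 evaluable (39 per arm); 10% dropout; 88 enrolled (44 per arm); analysis at two-tailed 0.05.

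**Assumed input.** The control rate is not stated, so it is back-solved below.

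**1. The plan's own figures.** The pooled two-proportion formula is

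n per arm = [z_α √(2p̄(1−p̄)) + z_power √(p1(1−p1) + p2(1−p2))]² / (p1−p2)².

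With p1 = 0.92, p2 = 0.70, p̄ = 0.81, z_α = 1.645 and z_power = 0.842:

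- √(2 × 0.81 × 0.19) = 0.5548
- √(0.0736 + 0.21) = 0.5325
- n = (1.645 × 0.5548 + 0.842 × 0.5325)² / 0.22² ≈ 38.3, so 39 per arm and 78 in total.

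Thus 78 reproduces at a control rate of about 0.70. Other methods imply 0.67 (continuity-corrected), 0.68 (Fisher exact) or 0.71 (arcsine). The dropout step also reproduces: 78/0.9 = 86.7, rounded up to 87, then 88 for equal arms.

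**2. Power at the declared two-sided level.** A check that needs no control rate: a design with 80% power at one-sided 0.05 has two-sided power of about Φ(1.645 + 0.842 − 1.960) = 70.1%.

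With the rates put in, power = Φ{[(p1−p2) − z_α √(2p̄(1−p̄)/n)] / √([p1(1−p1) + p2(1−p2)]/n)}. At n = 39 the two square roots are 0.0888 and 0.0853:

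- one-sided: (0.22 − 1.645 × 0.0888)/0.0853 = 0.87, power 80.7%
- two-sided: (0.22 − 1.960 × 0.0888)/0.0853 = 0.54, power 70.5%

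Two-sided power is 69.8% with a continuity correction (control 0.67) and 70.8% with Fisher's exact test (control 0.68). For two-sided 80% power at 0.92 against 0.70, the formula in step 1 with z_α = 1.960 gives 48.7, so 49 per arm and 98 evaluable.

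**3. Power under ITT with LOCF.** All 44 per arm are analysed. If a fraction d of each arm has no week-12 score, the rates become (1−d) × 0.92 and (1−d) × 0.70. Two-sided power by the pooled formula:

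| Lost before week 12, each arm | Rates compared | Power |
|---|---|---|
| 0% | 0.920 vs 0.700 | 75.8% |
| 5% | 0.874 vs 0.665 | 64.8% |
| 10% | 0.828 vs 0.630 | 55.3% |

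For the last row the two square roots are 0.0948 and 0.0924: (0.198 − 1.960 × 0.0948)/0.0924 = 0.13, power 55.3%. Across the other implied control rates and tests this row runs from 52% to 56%.

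**The case against.** Four points can be made in the plan's defence.

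**The word one-sided may be the error, not the calculation.** A two-sided 0.05 calculation by the same formula also gives 39 per arm, at a control rate of 0.665. With no control rate stated, the arithmetic cannot tell a one-sided calculation from a misdescribed two-sided one. This stands: the fall to 70% holds only if 78 was derived as the text says. The present wording favours that reading, and on the other reading the sample size paragraph still has to be corrected.

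**The 55% is one end of a range.** A reader might take the trial's power to be 55%. The protocol does not support that as a headline. It gives the 10% dropout no time point, follow-up runs to week 48, and losses after week 12 do not touch the primary outcome. The figure also needs equal loss in both arms and the back-solved control rate.

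**Not every dropout is a non-responder.** A patient who stops treatment may still be assessed at week 12. The plan never states in words that dropouts count as failures; this follows from LOCF and the visit schedule, and only for patients with no week-12 score. If the pre-trial 92% already counted dropouts as failures, scaling it by 0.9 counts them twice. Both limits stand.

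**The β = 0.80 is a label.** A reader might infer 20% power. At 92% against 70% that would take about 5 per arm, which does not fit 78. It is an editorial slip and changes no number here. The control rate may likewise be stated in a full protocol that is not shown, so asking for it is a request.

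None of this removes the conflict between the two sidedness statements.

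**Conclusion.** The point holds in conditional form.

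- **Firm:** the sample size is described as one-sided at 0.05 and the analysis as two-tailed at 0.05, and the protocol does not reconcile them.
- **Firm if 78 was computed one-sided as stated:** two-sided power with 78 evaluable patients is about 70%, a loss of about 10 percentage points that hardly depends on the missing control rate.
- **Scenario only:** with 44 per arm under ITT/LOCF, two-sided power lies between about 76% and 55% as loss before week 12 goes from 0% to 10%. This assumes a 70% control rate, equal loss in both arms, and a 92% not already reduced for dropout.

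On the stated derivation, even full retention of 88 patients leaves two-sided power below 80%. The correction matters because the power figure governs how a null primary result is read.

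**What to change.** Keep 88 patients and the two-sided 0.05 test. In the sample size paragraph:

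1. Say which calculation produced 78, one-sided or two-sided, and bring it into line with the analysis section.
2. State the assumed control response rate.
3. Write power = 0.80 (β = 0.20), as an editorial correction.
4. Replace the 80% claim with the two-sided power delivered. If 78 was one-sided with a control rate near 70%, that is about 70% with 78 evaluable, and 55% to 76% under ITT/LOCF depending on loss before week 12, with the assumptions written beside it. If the answers to items 1 and 2 differ, recompute these figures.

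Do not move the analysis to one-sided 0.05 to recover the stated power.

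The cost is wording and a less favourable power statement; no patients, visits or procedures are added. Restating the power does not raise it. As recruitment is under way, the change should be made before outcome data are analysed.
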